### *Patient replacement procedures*

Patients in this study who prematurely discontinue from the study will not be replaced.

## **9. TREATMENT OF PARTICIPANTS**

### **9.1 Description and justification for the treatments**

Information concerning the theory and development of the behavioural intervention is detailed in the 'Rationale and Background' section, and is summarised here.

#### *Name:*

- (1) iBASIS-VIPP
- (2) Treatment as usual

#### *Treatment schedule:*

Participants in the 'iBASIS-VIPP' group will receive 10 therapy sessions over a period of 5 months. Parents will be asked to undertake 30 minutes home practice with their infant daily. The 'Treatment as Usual' group will receive current treatment protocol offered within community health services, which varies considerably and may include a referral to a developmental paediatrician, a wait-list period (2-3 months), invitation to parent information sessions, and speech pathology assessment and intervention.

### **9.2 . The medications/interventions permitted during the trial.**

At the outset of the study, parents/carers will be asked to report all medications the child is taking, including the reason for taking the medication and duration for which medication has been taken to date. Participation in this trial does not prevent participants' seeking behavioural therapy outside of the trial framework. The nature and quality of any outside therapy and medications received will be recorded at the Follow-up Assessments.

### **6.3 Procedure for monitoring participant compliance**

Compliance in the 'iBASIS-VIPP group' will be monitored via a compliance checklist completed by the Research Therapist at each face-to-face session, and by the parent/caregiver following each daily practice session.

## **10. ASSESSMENT OF EFFICACY**

## 7.1 Specification of efficacy parameters and methods and timing for assessing and recording

Unless otherwise specified, all efficacy parameters will be recorded in source format. This will then be entered into an electronic database where it will be stored alongside participant's ID numbers. The database will be regularly checked for accuracy, and source documents will be retained to clarify any issues.

Autism Observation Scale for Infants will be used to measure the severity of autistic symptoms.  
*Method of Assessment:* Researcher-administered semi-structured play assessment with infant. Scored from video by researcher with demonstrated high level reliability, who is blind to treatment group.  
*Timing of assessment.* Baseline, Follow-up Assessment 1.

The Toddler Module of the Autism Diagnostic Observation Schedule – Second Edition will be used to measure the severity of autistic symptoms.

*Method of Assessment:* Researcher-administered semi-structured play assessment with toddler. Scored from video by researcher with demonstrated high level reliability, who is blind to treatment group.  
*Timing of assessment.* Follow-up Assessment 2 and 3.

The Manchester Assessment of Caregiver-Infant Interaction will be used to measure the quality of parent-infant interactions.

*Method of Assessment:* Parent-Infant free play interaction sample. Scored from video by researcher with demonstrated high level reliability, who is blind to treatment group.  
*Timing of assessment.* Baseline, Follow-up assessments 1, 2 and 3.

The Mullen Scales of Early Learning will be used to assess cognitive and motor ability.  
*Method of Assessment:* Researcher-administered standardised developmental assessment. Scored live by researcher administering the assessment.  
*Timing of assessment.* Baseline, Follow-up assessments 1, 2 and 3.

The Vineland Adaptive Behavior Scales – 2nd edition will be used to assess daily functional skills.

*Method of Assessment:* Caregiver-report questionnaire. Scored by researcher.  
*Timing of assessment.* Baseline, Follow-up assessments 1, 2 and 3.

The MacArthur-Bates Communicative Development Inventory will be used to assess early language development.

*Method of Assessment:* Caregiver-report questionnaire. Scored by researcher.  
*Timing of assessment.* Baseline, Follow-up assessments 1 (WG form), and 2 and 3 (WS form).

## [name] et al. Trial Protocol

Effect of pre-emptive intervention on developmental outcomes for infants showing early signs of autism: A randomized clinical trial of outcomes to diagnosis

The Parent Sense of Competence will be used to assess parenting self efficacy.

*Method of Assessment:* Caregiver-report questionnaire

Scored by researcher.

*Timing of assessment.* Baseline, Follow-up assessments 1, 2 and 3.

Clinical ASD diagnostic outcome will be assessed by experienced independent clinicians.

*Method of Assessment:* Independent clinician review of collected data.

Scored by independent clinicians

*Timing of assessment.* Follow-up assessment 3.

## 7.2 Methods for analysing efficacy parameters

This is detailed in section 'Statistical analysis plan'.

# 8 ASSESSMENT OF SAFETY

## 8.6 Summary of known and potential risks and benefits, if any, to research participants.

iBASIS-VIPP is a behavioural intervention that supports parents to interact with their infant to maximise social and communication development. The potential benefit of this behavioural intervention is a reduction in autistic symptomatology, and an increase in developmental abilities, such as language and social skills. There are no known risks of this intervention, and our previous studies have shown that this therapy is well tolerated by families. The safety issues for this trial are negligible.

## 8.7 The safety parameters and method for assessing and recording safety parameters.

### *Safety parameters*

Key safety parameters in the trial are occurrence of side effects, type of side effects, occurrence of adverse events, type of adverse event, occurrence and type of intercurrent illnesses across the trial.

### *Method for assessing and recording*

Parents/infants in the iBASIS-VIPP group will have face-to-face therapy sessions 10 times throughout the 5-month treatment period. Parents will also be asked to complete 30 minutes practice each day. At the end of each therapy session, the Research Therapist will record if there have been any adverse effects of the therapy noted during the session, as well as during the period since the last testing session. This will be recorded on the Case Report Form completed by the Research Therapist.

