### 4.10 Criteria for termination of the trial

Discontinuation criteria for the trial reflect guidelines set out by the TGA. The trial will be terminated in the case that support for the trial is withdrawn from the HREC or sponsor. This includes the following possibilities:

- Evidence of significant deviation from the trial protocol that may threaten wellbeing of participants;
- Evidence that allowing the trial to continue carries an unacceptable risk of death, serious injury or illness to participants;
- Evidence that one treatment proves to be so much better or worse that to continue would disadvantage one group of participants;
- Evidence that conduct of the trial is in breach of the law.

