## **8.9 The procedures for eliciting reports of and for recording and reporting adverse events. Include definitions of adverse events.**

We define an adverse event as any untoward medical occurrence in a patient or clinical investigation subject associated with the experimental treatment. The treatment protocol is focused solely on teaching parents how to modify their interactions with their infants, and therefore we believe the risk of any adverse events is extremely low. Caregivers will be provided with monitoring forms at the outset of the study to record any side effects they believe may be associated with the treatment. These forms will provide space to record side effects daily if needed.

Any adverse event will be reported to the PMH and LTU Human Research Ethics Committees in a detailed, formal written report, which will identify participants involved by study code rather than name or address. These reports will include an assessment of the severity and causality of the adverse event in relation to the treatment protocol (see Table 4), as well as detailed information regarding the steps taken by the Study Team with regard to both the treatment protocol and the participant involved.

*Supplementary Table 4.* The assignment of causality for each AE should be made by the investigator responsible for the care of the participant based on the definitions in the table below.

| Relationship   | Description                                                                                                                                                                                                                                                                                                   |
|-----------------------|----------------------------------------------------------------------------------------------------------------------------------------------------------------------------------------------------------------------------------------------------------------------------------------------------------------------|
| Unrelated      | Sufficient information exists to indicate that the aetiology is unrelated to the treatment protocol.                                                                                                                                                                                                                 |

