## **8.10 The type and duration of the follow-up of participants after adverse events.**

Adverse events will be monitored by the Research Therapists at each iBASIS session, which take place at fortnightly intervals during the 5-month treatment period. If an adverse event is reported by the caregiver, infant wellbeing will be followed up by study medical staff through phone calls and visits as needed (depending on the nature of the adverse event). Participants will be made

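### Adverse events are actively asked about only at iBASIS sessions and are defined by association with the experimental treatment, so infant harms cannot be compared between arms on like data

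*Supplement*

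**What the plan says.** All references are to the final protocol, Version 3.

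- **What is to be assessed.** Section 8.7 lists side effects and adverse events as key safety parameters, together with "occurrence and type of intercurrent illnesses across the trial".
- **How it is recorded.** The method under the same section concerns the intervention arm: "Parents/infants in the iBASIS-VIPP group will have face-to-face therapy sessions 10 times throughout the 5-month treatment period". It continues: "At the end of each therapy session, the Research Therapist will record if there have been any adverse effects of the therapy". The enquiry also covers the interval since the previous contact, and the result goes on the therapist's case report form. Section 8.10 repeats the arrangement: "Adverse events will be monitored by the Research Therapists at each iBASIS session, which take place at fortnightly intervals during the 5-month treatment period".
- **What counts.** Section 8.9 defines an adverse event as "any untoward medical occurrence in a patient or clinical investigation subject associated with the experimental treatment". It also gives caregivers a form at the start of the study for side effects that they attribute to the treatment. The form is not expressly restricted to one arm.
- **How cause is graded.** Supplementary Table 4 runs from 'Unrelated' and 'Unlikely' through 'Possible' and 'Definitely' to 'Not assessable'.
- **How the information may be used.** One ground for termination in Section 4.10 is "Evidence that one treatment proves to be so much better or worse that to continue would disadvantage one group of participants". Section 8.8 has an independent committee review cumulative data, including safety, every six months.

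**The concern.** A control family never attends an iBASIS session, so the only active enquiry cannot reach it. The person who asks also delivers the therapy, knows the allocation, and is asked to record effects of that therapy rather than everything that happened. The definition then adds a causal filter that an event in a control infant can hardly pass.

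The safety record would therefore reflect how events were found as much as how often they occurred. A count by arm could show an excess in iBASIS because only that arm was asked. Alternatively, the therapist's filter could leave few or no events and no control rate to judge them against. Neither result would tell the monitoring committee whether infant illness or other untoward events differ between arms. The analysis plan is a separate document and is not shown, but it could not repair this, because events that were never collected cannot be analysed.

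**Working it through.** The plan states no figure to reproduce. The check counts scheduled enquiries, asks whether any other source fills the gap, and compares the safety passages with one another.

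**1. Scheduled enquiries.** Inputs: 66 families per arm (Section 10.2) and 10 sessions (Section 8.7).
- iBASIS: 66 × 10 = 660 at most.
- Treatment as Usual: none described, so 66 × 0 = 0.

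These are planned contacts, not missed events.

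**2. Time without scheduled enquiry.** Therapy starts within two weeks of baseline (Section 4.9, treatment phase) and lasts five months, so it ends at about 5 to 5.5 months. Follow-up 3 is at 24 months.
- 24 − 5.5 = 18.5 months and 24 − 5 = 19 months, or 77% to 79% of follow-up, with no scheduled enquiry in iBASIS.
- For Treatment as Usual the uncovered period is all 24 months.

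**3. Other sources that might fill the gap.**

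| Source | Arms | What it gives |
|---|---|---|
| Caregiver monitoring form (8.9) | Not restricted by arm | Passive; only side effects attributed to the treatment |
| DASS (Supplementary Table 3; 8.10) | Worded for any parent; baseline and three follow-ups | Parental depression, anxiety and stress; nothing on the infant |
| Monthly diary (4.7, Treatment as Usual) | Stated for Treatment as Usual; for iBASIS, contact is to be quantified but no diary is named | Contact with health professionals |
| Outside therapy and medication at follow-ups (9.2) | Both | Treatments received, not events |
| Family questionnaire (Supplementary Table 2) | Both; baseline and three follow-ups | No adverse-event item described |

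None is a cause-neutral record of infant events gathered in the same way in both arms.

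**4. Definition against grading.** If association with the experimental treatment is part of being an adverse event, an event graded 'Unrelated' is not an adverse event. The definition and the scale cannot both be applied as written.

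**5. Parameter against method.** Intercurrent illness throughout the trial is a key safety parameter. The method asks only about effects of the therapy, in one arm, for five months. No described procedure collects intercurrent illness as such.

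**6. Illustration, on assumptions not in the documents.** Let the true proportion of infants with an event be p in both arms, with iBASIS recording all of them and Treatment as Usual a fraction c. Expected recorded counts are 66p and 66pc.

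| p | iBASIS | Control, c = 0.5 | Control, c = 0.25 |
|---|---|---|---|
| 10% | 6.6 | 3.3 | 1.7 |
| 20% | 13.2 | 6.6 | 3.3 |
| 30% | 19.8 | 9.9 | 5.0 |

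Unequal capture alone would thus produce a two- to fourfold apparent excess in iBASIS. With c = 1 the counts are equal. I attach no false-positive rate, because the protocol plans no significance test on adverse events.

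**The case against.** The strongest reply is proportionality. Section 8.6 describes a parent-coaching intervention with no known risks, the aims in Section 3.1 concern efficacy only, and no between-arm comparison of adverse events is promised. Collecting mainly harms attributed to treatment could be a deliberate choice. That argues for a light remedy. It does not explain why the protocol names intercurrent illness as a parameter and then describes no way to collect it, or why its definition contradicts its own causality scale.

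Three stronger readings are tempting, and the documents do not support them.

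- *Control families have no route at all.* The caregiver form goes out at the start and is not limited by arm, so a passive route may exist. What is missing is matching active capture.
- *Parental distress goes unrecorded.* The DASS is described for baseline and all three follow-ups, and a high score in any parent triggers contact from a clinically trained researcher.
- *The termination criterion cannot be applied.* It is not confined to adverse events. The committee also monitors efficacy, and outcomes rated blind in both arms could show one arm faring worse. Review of a serious event in Section 4.10 turns on its relation to trial participation, which covers both arms. Only the harm side of the criterion lacks a comparable adverse-event source.

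It is also fair to say that separate causality grading already exists in Supplementary Table 4. The fault lies in the definition that precedes it.

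**Conclusion.** The point holds in this form: active, scheduled adverse-event enquiry is described only at the 10 iBASIS sessions, by the unblinded therapist, and the definition practically excludes control-arm events. Infant adverse events and intercurrent illness therefore cannot be compared between arms on like data.

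In size, this is up to 660 planned enquiries against none described, and about 18.5 to 19 of 24 months without scheduled enquiry even in the iBASIS arm. The resulting bias cannot be quantified from the documents. The illustrative counts depend wholly on the assumed event rates and capture fractions, and the therapist's filter could also push recorded iBASIS events downwards.

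The conclusion rests on Section 8 describing the full collection procedure and on the forms containing no adverse-event item that the protocol leaves unmentioned. It concerns safety reporting and monitoring. It should be corrected, but it does not touch the primary or secondary efficacy analyses.

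**What to change.** 1. In Section 8.9, define an adverse event as any untoward occurrence in a participant, regardless of arm or cause, and leave causality to Supplementary Table 4.
2. Ask one identical item on adverse events and illness in both arms at the same times: in the monthly diary, and in the family questionnaire at Follow-ups 1 to 3. State explicitly that iBASIS families complete the diary too, as Section 4.7 implies, and that it runs for the same period in both arms.
3. Have the answers returned to the Trial Coordinator, who performs the randomisation and so already knows the allocation. This keeps them away from the blinded assessors.
4. Report events by arm from these common sources only, and list therapist-recorded events separately.

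The cost is one diary item, one questionnaire item and revised wording, with no extra staff. The drawback is a larger number of minor, unrelated events to process and grade.

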## 8.8 Details of the Data and Safety Monitoring Board, or equivalent.

An independent Data and Safety Monitoring Committee (DSMC) has been assembled to monitor the progress, safety and efficacy of this clinical trial and provide critical evaluation and recommendations to the study investigators and all sponsors of this trial. The members of the DSMC serve in an individual 'expert' capacity. The DSMC will meet every 6 months throughout

this trial and review cumulative study data to evaluate study conduct, the scientific validity and data integrity of the study including safety of this trial. Scheduled meetings will be supplemented with additional meetings or conference calls scheduled as needed.

## **8.9 The procedures for eliciting reports of and for recording and reporting adverse events. Include definitions of adverse events.**

We define an adverse event as any untoward medical occurrence in a patient or clinical investigation subject associated with the experimental treatment. The treatment protocol is focused solely on teaching parents how to modify their interactions with their infants, and therefore we believe the risk of any adverse events is extremely low. Caregivers will be provided with monitoring forms at the outset of the study to record any side effects they believe may be associated with the treatment. These forms will provide space to record side effects daily if needed.

Any adverse event will be reported to the PMH and LTU Human Research Ethics Committees in a detailed, formal written report, which will identify participants involved by study code rather than name or address. These reports will include an assessment of the severity and causality of the adverse event in relation to the treatment protocol (see Table 4), as well as detailed information regarding the steps taken by the Study Team with regard to both the treatment protocol and the participant involved.

*Supplementary Table 4.* The assignment of causality for each AE should be made by the investigator responsible for the care of the participant based on the definitions in the table below.

| Relationship   | Description                                                                                                                                                                                                                                                                                                   |
|-----------------------|----------------------------------------------------------------------------------------------------------------------------------------------------------------------------------------------------------------------------------------------------------------------------------------------------------------------|
| Unrelated      | Sufficient information exists to indicate that the aetiology is unrelated to the treatment protocol.                                                                                                                                                                                                                 |
| Unlikely       | When there is no reasonable temporal association between the treatment protocol and the suspected adverse event. The event could have been related to the patient's clinical state or concomitant treatment(s).                                                                                                      |
| Possible       | There is some evidence to suggest a causal relationship (e.g. because the event occurs within a reasonable time after administration of the treatment session). However, the influence of other factors may have contributed to the event (e.g. the participant's clinical condition, other concomitant treatments). |
| Definitely     | There is clear evidence to suggest a causal relationship, based on: temporal relationship to the treatment session                                                                                                                                                                                                   |
| Not assessable | When causality is, for one reason or another not accessible, e.g. because of insufficient evidence, conflicting data or poor documentation                                                                                                                                                                           |

## **8.10 The type and duration of the follow-up of participants after adverse events.**

Adverse events will be monitored by the Research Therapists at each iBASIS session, which take place at fortnightly intervals during the 5-month treatment period. If an adverse event is reported by the caregiver, infant wellbeing will be followed up by study medical staff through phone calls and visits as needed (depending on the nature of the adverse event). Participants will be made

